### Sample size and power calculation

Site-specific admissions data previously published trial data, and data from the PICU Up! pilot multicenter trial were used to conservatively estimate that an average of 8 patients/cluster/month will be eligible for inclusion for data collection [24]. In the proposed stepped-wedge design, with two hospitals switching at each of the five steps, a total of 180 months of observation (90 months control/90 months intervention) will be available for analysis. Therefore, 720 patients are expected to be included in the baseline period and 720 in the intervention (post-implementation) period. The power calculation accounted for the clustered nature of the study design and the confounding effect of time using preliminary data obtained from our multicenter pilot trial [46]. Specifically, 1000 hypothetical stepped-wedge trials were simulated assuming patients within hospitals would be correlated with an intra-class correlation (ICC) of 0.01 and allowed the days AVF to day 21 to decline linearly over time (month 1’s mean (variance) of 13.2 (26.4) days AVF to day 21, with a monthly decline of 0.1 days) with a fixed effect of the intervention that is constant over time. Given the design, the anticipated sample size, type I error of 5%, and power of 80%, a ≥ 1.8-day improvement in mean days AVF to day 21 will be detectable between the intervention and control period, which is a clinically meaningful reduction in the duration of mechanical ventilation [29–31].

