### Statistical methods

#### Patient-level outcomes

Descriptive statistics for continuous variables will be presented as the mean ± standard deviation and quantiles and categorical variables will be expressed as percentages. The effect of the PICU Up! intervention on the clinical outcomes will be estimated using mixed-effects models that include indicators for both the implementation (3-month duration) and the intervention vs. control periods and incorporate features of the stepped-wedge design by including a random intercept defined for each site to account for clustering of outcomes within sites and a fixed effect of time (month, modeled as a natural cubic spline) to account for temporal trends in the outcomes over the period of the study [49]. Linear mixed-effects models will be used for the primary outcome where the coefficient for the indicator of intervention vs. control period directly estimates the mean difference in days AVF by day 21 comparing the intervention and control period. To account for potential violations of model assumptions, robust variance estimates will be used. Similar linear mixed-effects models will be used for the secondary outcomes. We expect that the distribution of the primary outcome and the secondary outcomes will be skewed; however, given the large sample size, the linear models should be robust for estimating the mean difference in these outcomes. Poisson log-linear mixed-effects models with the same random and fixed effects will be used as a sensitivity analysis for the linear mixed-effects models proposed above. Logistic mixed-effects models will be used for binary patient-level outcomes. For the ordinal outcomes, Pediatric Cerebral Performance Category and Pediatric Overall Performance Category, if sufficient data is present in each ordered category or if we collapse the 6 ordered categories into at least 3 categories, we will utilize multinomial models to evaluate the effect of the intervention. If the data suggest collapsing the ordered categories into only two categories, then binomial regression models will be used.

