The primary analysis for all outcomes will be unadjusted, that is, we will assume that patients enrolled in the study over time will be similar with respect to characteristics associated with the outcomes (e.g., age and severity of illness). Secondary analyses will include exploratory analyses to evaluate this assumption and the models (described above) will be extended to include an adjustment for key patient characteristics (e.g., age, admission diagnosis category, measures of baseline function such as PCPC, POPC, FSS). Analyses to detect significant differences in the intervention effect among sex/gender will be conducted. Additional secondary analyses will fit the models described above, including adjustment for the patient-specific measure of PICU Up! performance by separately including the measure of proportional performance (ranging from 0 to 1) and the binary indicator of a complete performance.

Statistical significance will be set at *p*-value < 0.05 using a two-sided hypothesis test for the primary outcome analysis; all secondary analyses will be considered exploratory with two-sided 95% confidence intervals reported. We will conduct missing data assessment/estimation, and if necessary, employ methods for imputation of missing data using the MICE package [50].

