#### Process evaluation

Online survey data will be summarized using descriptive statistics. The mean and standard deviation will be reported for continuous measures and frequency and percentages for categorical variables. Trends in performance within a PICU over time will be explored using spaghetti plots with locally weighted regression smoothers to explore the general trends over time across all PICUs. Mixed-effects Poisson models will be used to model the trends in performance over time via restricted cubic splines with a minimum of a random intercept defined at the PICU level. Subsequently, the models will include the hospital and PICU-level covariates, such as structural characteristics, staffing patterns, organizational traits, rounding practices, and the use of daily teamwork tools. The inclusion of such covariates will allow for the determination of whether variation in performance across the PICUs is partially explained by these PICU-level factors.

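### The Poisson sensitivity model for days AVF has no term for the twofold overdispersion in the protocol's own planning figures, so its intervals will be too short unless robust variance or a dispersion term is stated to apply

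*Protocol article*

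**What the plan says.** In the protocol article, Statistical methods, Patient-level outcomes, the primary analysis of days AVF is a linear mixed model. It has a site random intercept, a spline in month, and indicators for the implementation and intervention periods. The next sentence plans robust variance estimates as protection against violated model assumptions. After similar linear models for the secondary outcomes and a remark that the outcomes will be skewed, the text adds that "Poisson log-linear mixed-effects models with the same random and fixed effects will be used as a sensitivity analysis" for those linear models. It names no dispersion parameter and no variance estimator for the Poisson models.

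The planning distribution is in Sample size and power calculation: a "mean (variance) of 13.2 (26.4) days AVF to day 21, with a monthly decline of 0.1 days", with patients in the same hospital "correlated with an intra-class correlation (ICC) of 0.01". Outcome measures bounds days AVF between 0 and 20.

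The significance threshold is set "using a two-sided hypothesis test for the primary outcome analysis". Secondary analyses are exploratory, with 95% confidence intervals.

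In the process evaluation, performance is defined as proportions of patient days or of eligible elements. The corresponding part of Statistical methods says that "Mixed-effects Poisson models will be used to model the trends in performance over time via restricted cubic splines".

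**The concern.** A Poisson mixed model with a site intercept allows extra variation between sites only. Within a site and month it forces the patient-level variance to equal the mean. The protocol's own planning figures put that variance at twice the mean, and none of the effects carried over from the linear model can absorb the difference. Unless something else is done, the standard error of the intervention effect is too small.

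This matters because it is the only alternative model family that the article names for the primary outcome. Its purpose is to show whether the linear-model result depends on distributional assumptions. If its intervals are too short, it can seem to confirm a weak primary result, or to disagree with a null one, for no reason other than the wrong variance.

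**Working it through.** **Inputs from the protocol article.** Month-1 mean 13.2, variance 26.4, decline of 0.1 days per month and ICC 0.01 (Sample size and power calculation). Ten PICUs, two switching at each of five steps, 8 patients per cluster-month, 90 control and 90 intervention months (same section). Study length 21 months and a 3-month implementation period (Timelines).

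**The plan's own figures.** 180 cluster-months x 8 = 1,440 patients, as stated. The article gives no error rate or coverage for the Poisson analysis, so there is none to reproduce. Its power statement ("1.8-day improvement in mean days AVF to day 21 will be detectable" at 80% power) concerns the linear model and does not enter this check. A generalised-least-squares calculation for the same design put the 80% detectable difference at about 1.4-1.5 days, so on these inputs the stated 1.8 is conservative.

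**Step 1, dispersion ratio.** Ratio = variance / mean.
- Month 1: 26.4 / 13.2 = 2.00.
- Mid-trial, mean 12.2: 26.4 / 12.2 = 2.16.
- Month 21, mean 13.2 - 20 x 0.1 = 11.2: 26.4 / 11.2 = 2.36.

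The last two assume that the variance stays at 26.4. The article gives it for month 1 only.

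**Step 2, standard error.** Model-based Poisson SE / true SE = 1 / sqrt(ratio). At a ratio of 2 this is 1 / 1.414 = 0.71. At 2.16 it is 0.68.

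**Step 3, rejection of a true null at nominal 5%.** Rate = 2 x (1 - Phi(1.96 / sqrt(ratio))).
- Ratio 2.00: 16.6%.
- Ratio 2.16: 18.3%.
- Ratio 2.36: 20.2%. This would apply only if the whole trial had the last month's mean.

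**Step 4, simulation of the design.** Null trials were generated with the planned mean, variance and ICC, as negative binomial or as beta-binomial on 0-20, with 6,000 trials per scenario (Monte Carlo standard error about 0.5 points). Each was analysed with a Poisson random-intercept model with spline time and both period indicators. The layout assumed 3 control months before the first step and 3 months between steps, which gives the stated 90/90 split, with 8 patients in every cell.

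| Standard error used | Null rejection |
|---|---|
| Model-based, no decline | 16.6-16.9% |
| Model-based, 0.1/month decline | 17.6-17.7% |
| Cluster-robust, normal reference | 12.5-13.2% |
| Cluster-robust, t on 9 df | 8.2-8.8% |

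The model-based rows correspond to 95% interval coverage of about 82-83%. The true standard deviation of the estimate was 1.41-1.46 times the mean model-based SE.

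**Step 5, source of the excess.** With truly Poisson data (1,000 trials per scenario), model-based rejection was 6.2-6.6%, so the rise to 17-18% comes from overdispersion. Cluster-robust rejection on the same data was 12.7-13.8% with a normal reference and 8.5-9.8% with t on 9 df, much as in the table. What remains under robust variance is therefore a 10-cluster effect and not overdispersion.

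**The case against.** The strongest reply is that the same paragraph plans robust variance to guard against violated assumptions. Overdispersion is such a violation, and the Poisson models are introduced as a check on the models to which that sentence belongs. On that reading the overdispersion problem is gone. The article is also a condensed document, and the variance estimator of a sensitivity model could sit in an analysis plan that is not shown. This stands in part: a reader might infer that the planned analysis will reject a true null 17-18% of the time, but the text supports that only if model-based standard errors are used. It does not dispose of the point. The article names the Poisson family and lists what is carried over to it, and variance estimation is not on that list. Uncorrected robust variance with 10 clusters would also not restore 5%.

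Four stronger readings should be resisted.
- **A rate of 20-21%.** The 20% figure takes the last month's mean for the whole trial and holds the variance constant. A separate run of only 600 trials gave 20.8%, with a 95% interval from about 17.6%. The larger simulation gives 17-18%.
- **Inflated trial type I error.** No test is attached to this analysis, and overdispersion alone does not bias the Poisson point estimate.
- **A known loss in the process evaluation.** At an assumed 80% performance with independent days, the Poisson SE is 1 / sqrt(1 - 0.8) = 2.24 times the binomial SE. The article gives no performance level, and days within a patient are correlated, so the factor cannot be relied on.
- **A large excess at zero.** The article says that the outcomes will be skewed and gives no share of patients with 0 days.

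**Conclusion.** The point holds conditionally. The protocol names a model family that its own planning variance contradicts by a factor of 2, and leaves unclear whether the protection in the same paragraph extends to it. With model-based standard errors, the intervals are too short by a factor of about 1.4. The result rests on the month-1 variance applying roughly throughout, the assumed step layout and equal cell sizes. If the variance fell with the mean so that the ratio stayed at 2, the closed-form rate would stay at 16.6%. The consequence is confined to how the sensitivity analysis is read. It is worth correcting because the change is nearly free.

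The process-evaluation point is minor: measures defined as proportions fit a binomial-type model better than Poisson, but the size of the gain cannot be given from the documents.

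**What to change.** Do one of the following for the sensitivity analysis of days AVF, and state it:
1. Fit it as quasi-Poisson or negative binomial with the same fixed and random effects.
2. Keep Poisson and say that cluster-robust variance applies to it.

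In either case add a small-sample correction for 10 clusters. The simulation shows that a t reference on 9 df alone leaves 8.2-8.8%, so under option 2 a bias-corrected robust variance should be considered as well. The corrected versions were not simulated here, and the chosen one should be checked on the planned design.

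A proportional-odds model for the 0-20 count is a possible addition. It replaces the mean comparison with a cumulative odds ratio, so it is a trade-off and not a like-for-like check.

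For the process evaluation, model performance with a binomial or beta-binomial mixed model.

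The cost is a sentence or two of analysis-plan wording and a different model call, with no new data or patients. Intervals will be about 1.4 times as wide as model-based Poisson intervals, plus a little for the small-sample correction.

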**Secondary outcomes**	
Days alive and delirium- and coma-free (ADCF)	Days when the patient was alive, without delirium, and coma-free for 24 continuous hours during a calendar day^b,c,d^ through 21 days
Days alive and coma-free (ACF)	Days when the patient was alive, and coma-free for 24 continuous hours during a calendar day^b,d^ through 21 days
Days alive	Days when the patient was alive for 24 h during a calendar day^e^ through 21 days
Functional status	Pediatric Cerebral Performance Category and Pediatric Overall Performance Category scores assessed at the earlier of PICU discharge or day 21

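### The ordinal PCPC and POPC outcomes have no ordinal model named, and the observed data decide how many categories, and so which estimand, are analysed

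*Protocol article*

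**What the plan says.** The protocol article lists functional status among the secondary outcomes and defines it in Table 1 as "Pediatric Cerebral Performance Category and Pediatric Overall Performance Category scores assessed at the earlier of PICU discharge or day 21". Statistical methods, Patient-level outcomes, calls both scales ordinal and sets out two routes:

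- **Three to six categories.** The condition is "if sufficient data is present in each ordered category or if we collapse the 6 ordered categories into at least 3 categories"; in that case "we will utilize multinomial models to evaluate the effect of the intervention".
- **Two categories.** "If the data suggest collapsing the ordered categories into only two categories, then binomial regression models will be used".

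Neither route names a proportional-odds or cumulative-logit model. There is no threshold for sufficient data, no merge scheme, no cut-point, and no statement that merging will be settled on counts pooled over the control and intervention periods.

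The same section earlier assigns linear mixed models to the secondary outcomes in general. The later, specific sentences on PCPC and POPC govern these two scales.

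Two further statements set the stakes. The significance level applies "using a two-sided hypothesis test for the primary outcome analysis", while "all secondary analyses will be considered exploratory with two-sided 95% confidence intervals reported". Adjustment for "measures of baseline function such as PCPC, POPC, FSS" is planned as a secondary analysis; the main analysis is unadjusted.

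**The concern.** Two features cause difficulty.

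**Ordering.** On its plain reading, a multinomial model gives each non-reference category its own intervention effect: up to five contrasts for six levels, two for three levels. It does not use the fact that the levels are ordered. The reader gets several less precise odds ratios and no single answer on whether function shifted.

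**Data-dependent estimand.** The number of categories depends on what the data look like, and the estimand follows from it: five contrasts, two contrasts, or one odds ratio at a cut that is not named. Treatment period is known to everyone in this trial (Blinding), and the article does not say that the decision will be made without sight of the comparison. Collapsing to two levels also throws away information that an ordinal model would keep.

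Improved functional status is part of the stated objective of the trial, so a reader will look for a clear answer on it, even though the analysis is labelled exploratory.

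**Working it through.** The article gives no figure for PCPC or POPC, so there is none to reproduce. What follows sizes the two mechanisms. It does not test a stated number.

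**Inputs from the article.** Six ordered categories, hence five possible dichotomies. For sample size, "720 patients are expected to be included in the baseline period and 720 in the intervention (post-implementation) period".

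**Assumed inputs (not in the article).** Three category distributions, lowest to highest level:

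- flat: 1/6 each
- moderately skewed: 35/25/18/12/5/5%
- strongly skewed: 60/15/10/7/3/5%

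**1. Information kept by one dichotomy.** For a small common log odds ratio, relative to a proportional-odds analysis of all six levels, it is c(1−c) / [(1 − Σp³)/3], where c is the cumulative proportion at the cut and p are the category proportions.

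| Distribution | Σp³ | (1−Σp³)/3 | Best cut | Worst cut |
|---|---|---|---|---|
| Flat | 0.0278 | 0.3241 | c = 0.50: 0.2500/0.3241 = 77% | c = 1/6 or 5/6: 0.1389/0.3241 = 43% |
| Moderate skew | 0.0663 | 0.3112 | c = 0.60: 0.2400/0.3112 = 77% | c = 0.95: 0.0475/0.3112 = 15% |
| Strong skew | 0.2209 | 0.2597 | c = 0.60: 0.2400/0.2597 = 92% | c = 0.95: 0.0475/0.2597 = 18% |

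So 77-92% is kept at the best cut and 15-43% at the worst.

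**2. Cost of spreading one shift over several contrasts.** An effect with 80% power on 1 df at two-sided 5% has noncentrality (1.96 + 0.84)² ≈ 7.85. Putting that into a noncentral chi-square with more degrees of freedom gives:

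| df | Categories kept | Power |
|---|---|---|
| 1 | ordinal model | 80% |
| 2 | 3 | 71% |
| 3 | 4 | 64% |
| 5 | 6 | 56% (55.5%) |

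To return to 80%, the noncentrality must be 9.63 on 2 df (9.63/7.85 = 1.23 times the sample) or 12.83 on 5 df (12.83/7.85 = 1.63 times). These are joint tests, which the article does not specify; they serve as a scale for lost precision.

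**3. Simulation check.** 20,000 data sets per scenario, 720 against 720 independent patients, common odds ratio 1.3 (assumed), no clustering or time trend. Power was 0.70-0.80 for an ordinal 1-df test (Wilcoxon), 0.44-0.56 for the 5-df test, and 0.17-0.69 for a single dichotomy, depending on cut and distribution. With no effect, taking the smallest p-value over all five cuts rejected in 16-18% of data sets instead of 5%. That last figure is an upper limit for deliberate selection, which is not what the article describes.

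Because the simulation ignores clustering and time, its absolute power figures do not carry over to the stepped-wedge analysis; the contrast between methods is what it illustrates.

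**The case against.** **Multinomial may mean cumulative logit.** The article calls the scales ordinal and the categories ordered, and pairs multinomial with binomial in a way that could name response distributions. A cumulative-logit model is a model for a multinomial response. This stands as a possible reading, so it cannot be said that the ordering will certainly be discarded. It does not rescue the merging rule or the fall to two levels. A cumulative-logit model tolerates sparse levels, so most of the reason for collapsing goes.

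**The trigger is sparseness.** A reader might infer that the cut-point will be picked to favour the intervention. The article does not support that: its stated condition concerns how much data sit in each category, not the treatment contrast. Lack of blinding does not show that merging will be done by period, and cuts set on pooled counts would largely remove any inflation. A sparse-data rule would also tend to avoid cuts that isolate a small top group, where the worst retention figures arise. What remains is that the text does not require pooled, treatment-blind merging.

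**No test is planned.** A reader might take 56% as the power of the planned analysis. It is not: only the primary outcome is tested, and secondary results come with confidence intervals. The loss shows as wider intervals around several estimates.

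**Detail for the analysis plan.** Thresholds and link functions are often left to a statistical analysis plan, which may exist here. But the article states a rule under which the data choose the categories. A later document would have to replace that rule, not merely complete it.

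**Proportional odds is itself an assumption.** This stands. A multinomial model avoids it, and cut-specific checks are imprecise where categories are sparse.

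**Conclusion.** The point holds for a named but exploratory secondary outcome. The article calls PCPC and POPC ordinal, names no ordinal model, and lets the observed data set the number of categories and therefore the estimand. On the plain reading the ordering goes unused; on the looser reading of multinomial, the data-dependent merging and the avoidable loss from the binary fallback are left.

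The size can only be illustrated, because neither the category distribution nor an ordinal effect size is given. The information-retention range depends on the three assumed distributions and on proportional odds, and the loss from extra degrees of freedom applies only if the contrasts were tested jointly.

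The primary conclusion and its 5% error rate are untouched. The consequence is less precision and a less interpretable answer on functional status.

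**What to change.** In Statistical methods, Patient-level outcomes, replace the two model sentences for PCPC and POPC with these commitments:

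- Each scale is analysed on all six categories with a proportional-odds (cumulative-logit) mixed model, with the site random intercept, spline for month, and implementation and intervention indicators already planned. One common odds ratio is reported with its 95% CI.
- The data-dependent collapsing rule is deleted. If merging is needed for the model to fit, the scheme is fixed in advance or on counts pooled over periods, by someone blind to the comparison.
- Category frequencies by period and cut-specific odds ratios are shown as a check on proportionality.
- Adjustment for baseline PCPC and POPC stays as the secondary analysis already planned; this change does not need it in the main analysis.

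The cost is a few sentences and standard software, with no new data. The downside is reliance on approximate proportional odds, with a check that is imprecise in sparse categories. If an analysis plan already fixes the model and the categories, bringing the two documents into line is enough.

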#### Secondary outcomes

Secondary outcomes will include days alive and delirium- and coma-free (ADCF), days alive and coma-free (ACF), and days alive, as well as functional status at the earlier of PICU discharge or day 21, measured through Pediatric Cerebral Performance Category and Pediatric Overall Performance Category scores. If the patient was discharged from the PICU alive, all days following discharge will be considered days alive, delirium- and coma-free (Table 1).

**Table 1 Tab1:** Definition of outcome measures

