### Data collection and management

Identical, standardized data collection will occur during both the control and intervention phases. Data collection includes patient demographic, clinical, and rehabilitation data from the Epic electronic health record (EHR) from PICU admission through the earlier of day 21 or PICU discharge. The Data Coordinating Center (DCC) and CCC will provide oversight for all relevant study-related activities. The composition of the DCC and CCC are specified in Additional file 1. Data will be captured, managed, and exported using a secure, auditable, and HIPAA-compliant database (REDCap) with unique de-identified research participant identifiers [47]. The REDCap database will include automated data validation, range checks, branching logic, and designating fields as required. Data quality will be ensured through protocolized data collection, staff training and re-training on protocols, and auditing, independent of investigators and the sponsor. Auditing by the DCC includes initial and ongoing quality assurance procedures, periodic data cleaning, regular data queries, and PICU Up! performance feedback to sites [48].

The clinical trial will collect data on potential adverse events prospectively; this data will be reviewed daily, and reports will be made to the Data Safety Monitoring Board (DSMB), Institutional Review Board (IRB), and sponsor as required.

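### The primary analysis omits baseline covariates that the plan already intends to use, which gives up modest precision and a little protection against case-mix imbalance

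*Protocol article*

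**What the plan says.** The Patient-level outcomes section under Statistical methods fixes the choice: "The primary analysis for all outcomes will be unadjusted". The reason follows: "we will assume that patients enrolled in the study over time will be similar with respect to characteristics associated with the outcomes", with age and severity of illness as the examples.

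The word unadjusted refers to patient characteristics only. The primary linear mixed model keeps a random intercept for site, a natural cubic spline for month, and indicators for the implementation and intervention periods.

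The same section places both the check of the assumption and the covariate model among the secondary analyses, where the models "will be extended to include an adjustment for key patient characteristics (e.g., age, admission diagnosis category, measures of baseline function such as PCPC, POPC, FSS"). On the standing of those results it says: "all secondary analyses will be considered exploratory with two-sided 95% confidence intervals reported".

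Data collection and management describes what is available: "Data collection includes patient demographic, clinical, and rehabilitation data from the Epic electronic health record (EHR) from PICU admission". Functional status, a secondary outcome, is "measured through Pediatric Cerebral Performance Category and Pediatric Overall Performance Category scores" at the earlier of PICU discharge or day 21. Its main analysis falls under the same unadjusted rule.

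**The concern.** Units are randomised, not patients, and there are only ten of them, described under Study setting as differing in size and patient population. Nobody is blinded. Comparability of patients between periods is therefore not secured by randomising individuals, and the confirmatory test rests on an assumption that the plan examines only afterwards. If the adjusted and unadjusted models disagree, the unadjusted one carries the conclusion.

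Two things are at stake. The first is precision: variation in days alive and ventilator-free (AVF) that age, diagnosis or baseline function could explain stays in the error term. The second is protection: case-mix differences between control and intervention months are removed only so far as the site and month terms capture them.

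The omission is plainest for functional status, where PCPC and POPC at discharge are compared without the same child's baseline category, although baseline PCPC and POPC are named for the secondary model.

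**Working it through.** **Inputs.** From Sample size and power calculation: 8 patients per cluster-month, variance 26.4, ICC 0.01, two sites switching at each of five steps, 180 cluster-months (90 control, 90 intervention), and 1.8 days detectable at 80% power. From Timelines: 21 months, with 3 months of implementation per site. The design figure is not shown, so I took control periods of 3, 6, 9, 12 and 15 months and intervention periods of 15, 12, 9, 6 and 3 months, two sites each.

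**Plan's own figures.** The layout gives 2 × (3+6+9+12+15) = 90 months in each condition, and 180 × 8 = 1,440 patients. Both agree with the article. The 1.8 days does not reproduce. With normal critical values I get 1.37 to 1.49 days at equal site sizes. With t critical values on 8 df and the implementation months dropped, I get 1.62 to 1.70. The published figure came from a simulation not described in full and is on the cautious side. Nothing below depends on it.

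**Standard error.** Between-site variance is 0.01 × 26.4 = 0.264 and patient-level variance is 0.99 × 26.4 = 26.136. Site-month means at one site have covariance V = (26.136/8)·I + 0.264·J. The variance of the intervention coefficient is the matching diagonal element of (Σ X′V⁻¹X)⁻¹, where X holds the intercept, the month spline, and the implementation and intervention indicators. Covariates with explanatory power R² replace 26.136 by 26.136 × (1 − R²). R² is assumed.

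| R² | SE (days) | Fall in SE | Gain in information | Detectable difference, 2.80 × SE |
|---|---|---|---|---|
| 0 | 0.500 | – | – | 1.40 |
| 0.10 | 0.479 | 4% | 9% | 1.34 |
| 0.20 | 0.455 | 9% | 21% | 1.28 |
| 0.30 | 0.430 | 14% | 35% | 1.20 |

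The gain in information is (SE₀/SE)² − 1, for example (0.500/0.430)² − 1 = 0.35. This is what 9%, 21% or 35% more patients would buy if they came with proportionally more units. The fall is slightly less than 1 − √(1 − R²), which is 5%, 11% and 16%, because patient covariates are taken to leave the between-site variance unchanged.

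If power at 1.8 days is taken as the stated 80%, the SE ratios 0.956, 0.910 and 0.859 give Φ(2.80/ratio − 1.96) = 83%, 87% and 90%.

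**Case-mix shift.** As an illustration, suppose a diagnosis group whose mean differs by 4 days grows by 10 percentage points: 0.10 × 4 = 0.4 day (both values assumed). Place the shift δ = 0.4 in the intervention months of the affected sites only. The estimate then moves by the intervention element of (Σ X′V⁻¹X)⁻¹ Σ X′V⁻¹δ.

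- One pair of sites, earliest to latest switch: 0.133, 0.101, 0.075, 0.056 and 0.034 day.
- One site: half of these, about 0.02 to 0.07 day.
- All ten sites, each at its own switch: the pair values sum to 0.40 day, so the shift passes through in full.

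**Drift.** Linear or smooth seasonal drift common to all sites moves the estimate by less than 0.01 day. Site-specific linear drift with an SD of 1 day over the trial adds about 0.09 day of error SD, which raises 0.500 to √(0.500² + 0.09²) = 0.508.

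**The case against.** An unadjusted analysis of a stepped-wedge trial is legitimate. The switch order is randomised, so site-specific seasonality adds noise and not systematic bias. The site intercept and month spline deal with stable site differences and shared trends. The article already plans both a check of the assumption and an adjusted model, so the question is only which of two planned models is called primary. No R² is given, and the rebuilt model does not show the trial to be short of power. All of this stands, and it keeps the point at the level of a recommended improvement.

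Several stronger readings are tempting, but the document does not support them:

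- **A case-mix change at one or two sites goes straight into the estimate.** It does not. The figures above show a small fraction of it passing through.
- **Unblinded staff choose who enters.** Ethics and dissemination describes a waiver of consent so that all eligible patients are captured, and entry turns mainly on ventilation status on day 3.
- **The intervention itself alters who is still ventilated on day 3, and adjustment would cure that.** The route is possible, because the intervention reaches every PICU patient through daily rounds, and a shift of this kind could occur at all sites. The document does not show that it happens, and measured baseline covariates would correct it only in part.
- **The functional-status model ignores category order.** The article says "we will utilize multinomial models to evaluate the effect of the intervention", but it also calls these outcomes ordinal. The link may be settled in a statistical analysis plan that is not shown.

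**Conclusion.** The point holds as a question of efficiency, with a modest gain in robustness. The protocol makes its only confirmatory test depend on an untested assumption ("we will assume that patients enrolled in the study over time will be similar") and leaves out covariates that it already plans to model.

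The cost is a standard error about 4% to 14% larger than it need be, for assumed R² of 0.10 to 0.30. If R² is only 0.05 the difference is about 2%. Bias from a local case-mix shift is small: at most 0.133/1.8 = 7% of the target difference for one pair in the illustration, against 0.4/1.8 = 22% if every site shifts as it switches. The document gives no sign that the latter will occur.

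These figures rest on the inferred layout, equal site sizes, an ICC of 0.01, and covariates that act on patient-level variance only. Dropping the implementation months leaves the picture the same (SE 0.521, falling by 5%, 9% and 15%).

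It would be wrong to infer that the planned analysis is invalid or that the trial is underpowered.

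**What to change.** By documented amendment, before outcome data are examined by period:

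1. Make primary the linear mixed model already described (site intercept, month spline, implementation and intervention indicators) plus a short fixed list of covariates measured before exposure: age, admission diagnosis category, baseline PCPC/POPC or FSS, and admission severity if it is collected. The article names severity as related to outcome but does not include it in its example adjustment list, so its availability needs confirming.
2. Keep the model without patient covariates as a sensitivity analysis.
3. For discharge PCPC and POPC, include the baseline category in the main model.

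In the linear model the coefficient remains a mean difference in days AVF, so the question being answered does not change. For PCPC and POPC the odds ratio becomes conditional on baseline category and should be reported as such.

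The cost is more than a wording edit. Enrolment began in August 2022 and the DSMB reviews intervention effects every 12 months, so the change should be dated and made by people who have not seen outcomes by period. Missing covariates need handling, for which MICE is already named. No added patients or visits are needed for the covariates already named.
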